### Exploratory analysis

Device adherence, objective markers of bronchial and systemic allergy and inflammation, lung function measures, asthma and rhinitis control, quality of life and indoor air quality assessments will be analysed to determine factors that may be associated with treatment response.

### Study visit schedule

The study visit schedule consists of two visits during the screening period to assess eligibility and four visits during the 12-month treatment period at 3-month intervals, 3, 6, 9 and 12 months post-randomisation (Table 1).

**Table 1 Tab1:**
[figure not shown]
Study visit schedule

^i^Informed Consent will be sought for the main trial and qualitative studies (during internal pilot and at completion of the follow-up period) at Screening Visit 1

^ii^Post Randomisation Telephone Review after 1 month (+/- 3 days) to review device usage and check device related technical issues have been addressed

^iii^Severe Exacerbation Reporting. Participants will report severe exacerbations to their local trial team as soon as possible throughout the follow-up period

^iv^Serum Specific IgE only required if Skin Prick Tests not available

^v^Post-Trial Provision Period refers to treatment with an active TLA device free of charge including filters and technical support over a 4 year period

^vi^Adult Carer / Partner participation in selected cases is entirely optional and will not influence participant’s eligibility for inclusion in the trial

^vii^Installation within 10 working days of Randomisation

^viii^Device Exchange / Removal within 10 working days of last study visit or focus group involvement whichever comes last

At the first visit (Screening Visit 1), after consent, the following information is collected: participant’s demographics, past medical history, occupational history, participant’s asthma history including exacerbation history and a review of current asthma symptoms and current medications, bronchodilator reversibility testing and allergy testing (skin prick tests or serum specific IgE) are performed, Blood samples are taken for total IgE and peripheral blood eosinophil count. Participants are asked to complete an ACQ and are issued with an electronic peak expiratory flow meter for use during the trial.

At the second visit (Randomisation Visit 2), the asthma control diary and peak flow diary is collected. Participants complete the following questionnaires: ACQ, AQLQ, EQ-5D-5L, WPAI-A, SNOT-22 and the LASER Indoor Air Quality Questionnaire. Pre-bronchodilator spirometry is performed, and FENO is measured. Allergy testing is performed if this was not possible at Screening Visit 1. Participants are issued with the following: (i) a LASER diary for daily recording of overnight device use (hours,) additional device use (hours,) time off work as a result of asthma (hours) and dose of oral corticosteroids (mg); (ii) exacerbation diary cards for completion at the onset of an exacerbation throughout the trial (including PEF, steroid dose, reliever medication use and nocturnal wakening); and (iii) an Asthma Control Diary for completion prior to their next follow-up visit (including morning pre-bronchodilator PEF.) Participants will also be issued a Resource Use Log and a participant identification card.

Participants whose partner and/or carer wish to participate in the trial are asked to attend together for either visit 1 or visit 2 so that Carer/Partner consent can be obtained. Partners are asked to consent for participation in the qualitative study and carers are asked to consent to completion of questionnaires at visit 2 and at the 12-month follow-up visit (ACQoL and WPAI-CG).

One month following the Randomisation Visit 2, participants are contacted by telephone for their 1-month telephone review, where device delivery and installation will be confirmed, and any problems with the device or trial can be addressed.

Follow-up visits are held at 3-, 6-, 9- and 12-months post-randomisation. Participants collect 2 weeks of peak flow recordings and an asthma control diary prior to each follow-up visit. At the follow-up visits, participants complete questionnaires (ACQ, AQLQ, EQ-5D-5L, SNOT-22 and WPAI-A) and perform pre-bronchodilator spirometry and FENO. At each follow-up visit, exacerbation history is reviewed along with self-reported device usage using the LASER diary and healthcare resource use log. Device reported use is also documented at each follow-up visit.

At the 12-month follow-up visit, a GETE questionnaire will also be completed.

Participants will report severe exacerbations to their local trial team throughout the trial, and if possible, face-to-face reviews will be arranged to corroborate the diagnosis of a severe exacerbation. If a face-to-face review is not possible, then a telephone review will be recorded.

### Safety reporting

Participants will be asked about the occurrence of any adverse events (AEs) (using the definition given in the International Conference on Harmonisation - Good Clinical Practice (ICH GCP) [28]) at each follow-up visit and will be asked to report AEs to their local trial team between visits. Only AEs that have a reasonable possibility of being attributable to the device (that is an Adverse Device Effect (ADE)) and any other AE considered to be of clinical significance by the local principal investigator as causing harm to the patient will be recorded. ADEs also include any event resulting from insufficiencies or inadequacies in the instruction for use or deployment of the device and includes any event that is a result of a user error.

Events exempt from recording are those related to worsening asthma control or the main study outcomes, namely the following:An increase in rescue medication usage.Additional courses of steroids for asthma exacerbations.Increased unscheduled healthcare usage including GP and Emergency Department visits for deteriorations in asthma control.Time off work, College or University due to worsening asthma control.Hospitalisation due to asthma exacerbation.Increased number or intensity of asthma exacerbations.

All serious adverse events (SAEs) and serious adverse device effects (SADEs), defined as any untoward medical occurrence seen in a patient that can be attributed wholly or partly to the device and resulted in any of the characteristics or lead to the characteristics of a Serious Adverse Event) will be recorded on a serious adverse event form and be reported within 24 hours to the Oxford Respiratory Trials Unit (ORTU). A second medical assessment of all reported SAE/SADEs will then be performed, and if considered by either the PI or ORTU to be possibly, probably or definitely related to the device (SADE), will be expedited to the Sponsor, REC and device manufacturer within 7 days of ORTU becoming aware of the event, if fatal or life threatening, or otherwise within 15 days. Listings of adverse events will be provided to the Data Safety Monitoring Committee (DSMC) and the Sponsor when requested. The DSMC will report to the TSC and Sponsor regarding the safety profile of the trial.

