#### Secondary aims

The secondary aims include assessing the impact of nocturnal TLA treatment on additional aspects of asthma control including symptoms, reliever use, airway obstruction, and on the risk of future adverse asthma outcomes, including an accelerated decline in lung function and the side-effects of treatment over the 12-month period. The impact of the treatment on the quality of life of the patients and their carers will be assessed using the Asthma Quality of Life Questionnaire (AQLQ) and a generic health-related quality of life questionnaire (EQ-5D-5L) for trial participants and the Adult Carer Quality of Life questionnaire (ACQoL) for participant’s adult carers. The impact of the treatment on both the NHS and social costs, that is, healthcare utilisation, will be measured using patient questionnaires and a review of patient’s records and education/work days lost, which will be assessed using the Work Productivity Activity Impairment questionnaire (WPAI) in both participants and their adult carers. These data will be further analysed to assess the cost-effectiveness of the intervention, using a cost-utility analysis to determine the incremental cost per quality-adjusted life year (QALY) gained. Finally, we aim to qualitatively evaluate the perceptions, values and opinions of the participants and their partners relating to the device to identify potential modifications that may improve patient acceptance and will inform future implementation of the device within the NHS.

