### Study intervention

The active TLA device (Airsonett™) significantly reduces nocturnal allergen exposure by filtering ambient air through a high efficiency particulate air filter, slightly cooling (0.5-0.8° C) and ‘showering’ it over the participant during sleep (Fig. 2). The reduced temperature allows the filtered air to descend in a laminar stream, displacing allergen-rich air from the breathing zone reducing allergen exposure without creating draft or dehydration. The device is installed next to the participant’s bed by a qualified engineer from the company. The device is pre-programmed to turn on and off at times specified by the trial participant but can be turned on and off by manual override if the participant wishes to use the device for an extended period or turn the device off when not in use. The device is easy to use with no identified safety concerns in previous trials. The device is CE marked and licensed for use in the UK for allergic asthma. The device uses the same amount of electricity as a 60 W light bulb and has an anticipated life-span of 5 years with filter changes required every 6 months. Participants will be asked to sleep under the device for at least 5 nights per week except when on holiday during the 12-month treatment period. Participants will record whether they have used the device or not and number of hours used on a daily basis, recorded in a ‘LASER’ diary. Any additional hours used during the day will also be recorded in the diary.

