### Interim analysis and criteria for early study termination

No interim analysis is planned; however, the DSMC will perform regular reviews of all study outcome and adverse event data to ensure that there is no difference in rates of hospitalisation or exacerbation in either group. The DSMC will determine final criteria for early study termination, which may be based on clear-cut evidence of worsened safety in one of the trial arms, and in the case of evidence beyond reasonable doubt of clear-cut benefit in the primary outcome measure, an effect size which would change clinical practice in the presence of the current literature and understanding of the disease area.

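### Non-serious adverse events are screened for device attribution or clinical significance before they are recorded, which leaves their comparison by arm incomplete and less sensitive

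*Protocol article*

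**What the plan says.** All references are to the protocol article.

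- **Elicitation (Safety reporting).** The question put at each follow-up visit is open: "Participants will be asked about the occurrence of any adverse events (AEs". Participants are also asked to report events between visits.
- **Recording of non-serious events (Safety reporting).** There are two routes in. The first is attribution: "Only AEs that have a reasonable possibility of being attributable to the device". The second is clinical significance: "any other AE considered to be of clinical significance by the local principal investigator as causing harm to the patient will be recorded". The local principal investigator is named for the second route. The section does not say who judges the first.
- **Exemption (Safety reporting).** "Events exempt from recording are those related to worsening asthma control or the main study outcomes". A list of asthma events follows.
- **Serious events (Safety reporting).** All are recorded, and relatedness is judged afterwards: "A second medical assessment of all reported SAE/SADEs will then be performed". That judgement decides expedited reporting, not whether the event is recorded.
- **Blinding (Randomisation and blinding).** Participants and study team do not know the allocation.
- **Use of the data (Interim analysis and criteria for early study termination).** The DSMC reviews outcome and adverse event data, and may act on "clear-cut evidence of worsened safety in one of the trial arms".
- **Related aim (Secondary aims).** Under the risk of future adverse asthma outcomes, the article lists effects "including an accelerated decline in lung function and the side-effects of treatment over the 12-month period".

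**The concern.** With randomisation and a placebo device, nobody has to decide in advance whether an event is due to the device: a difference in frequency between the arms shows it. Asking for a causality judgement before recording reverses that order. An unexpected effect of the device is the kind of event least likely to be thought attributable, and the Study intervention section describes a device with "no identified safety concerns in previous trials". If such an effect is also not judged clinically significant harm, it leaves no trace.

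Two things are at stake. A short or balanced list of non-serious events could reflect non-recording as much as absence of effect. And the DSMC would see only the admitted non-serious events, with thresholds that may differ across as many as 15 centres.

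**Working it through.** **1. Which events are lost.** Setting the Safety reporting rules side by side:

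| Type of event | Recorded as an adverse event? |
|---|---|
| Serious | Yes, relatedness judged afterwards |
| Non-serious, possibly due to the device | Yes |
| Non-serious, not thought due to the device, judged clinically significant harm | Yes |
| Non-serious, neither of these | No, although elicited |
| Listed asthma events | No, but exacerbations, steroid use and healthcare use are collected as outcomes |

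The gap is the fourth row. (Asthma hospitalisation is on the exempt list, while all serious events are to be recorded. Those two statements need reconciling, but that is a separate matter.)

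**2. Inputs for size.** The article gives no adverse event rate, no share of events that would pass the screen and no power for adverse events, so there is no figure of its own to reproduce here. The only inputs from the article are 222 participants and 10% dropout (Sample size): 222 × 0.90 = 199.8, or about 100 evaluable per arm. Everything else below is assumed.

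**3. Main illustration.** Assume true proportions with the event of p0 = 15% on placebo and p1 = 33% on the active device, and a share s of events recorded, equal in both arms because the screen is blind. The recorded proportions are s·p0 and s·p1. Power for a two-sided 5% Fisher exact test is the sum, over all pairs of counts (x, y), of Bin(x; 100, s·p0) × Bin(y; 100, s·p1), counting only pairs with p ≤ 0.05.

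| Share recorded | Recorded proportions | Difference | Power |
|---|---|---|---|
| 100% | 15% v 33% | 18 points | 82% |
| 75% | 11.25% v 24.75% | 13.5 points | 65% |
| 50% | 7.5% v 16.5% | 9 points | 43% |
| 25% | 3.75% v 8.25% | 4.5 points | 18% |
| 10% | 1.5% v 3.3% | 1.8 points | 3% |

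The ratio of the proportions stays at 33/15 = 2.2 throughout. An equal screen therefore does not push the ratio towards either arm; it removes information.

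**4. Other assumed rates.** With the normal approximation, power = Φ[(d − 1.96·se0)/se1], where d is the difference in recorded proportions, se0 = √[p̄(1 − p̄)(2/100)] with p̄ their mean, and se1 = √{[p0(1 − p0) + p1(1 − p1)]/100}, using recorded proportions throughout. Worked case, 20% v 35% with half recorded: proportions 10% and 17.5%, d = 0.075, p̄ = 0.1375, se0 = 0.0487, se1 = 0.0484. Power = Φ[(0.075 − 0.0955)/0.0484] = Φ(−0.42) = 34%.

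| True rates | 100% recorded | 75% | 50% | 25% |
|---|---|---|---|---|
| 10% v 25% | 80% | 66% | 47% | 25% |
| 20% v 35% | 66% | 50% | 34% | 18% |
| 30% v 45% | 59% | 42% | 27% | 15% |

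The pattern is the same in each row. The level depends entirely on the assumptions.

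**The case against.** The strongest case for the present rule is that it is a deliberate, low-burden choice for a CE-marked airflow device in a pragmatic trial. The attribution route asks only for a reasonable possibility and includes user error. The clinical-significance route admits events whatever their suspected cause. Assessors are blind. Serious events escape the screen, and the DSMC also sees outcome data that never pass through it. SNOT-22, AQLQ, EQ-5D-5L, spirometry and exhaled nitric oxide are measured in both arms at every follow-up visit. No powered comparison of non-serious events is planned, and every power figure above rests on assumed rates.

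Most of this stands, and it limits the point. It rules out several stronger readings that a reader might infer:

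- *That side-effects cannot be compared between arms.* They can, for serious events, possibly device-related events and clinically significant ones.
- *That the screen favours the active device.* Nothing in the article suggests that a blind screen would differ by arm.
- *That the DSMC's safety criterion rests only on screened data.* It also has serious events and all study outcomes, including hospitalisation and exacerbation rates.
- *That the rule plainly contradicts the secondary aim.* The side-effects phrase sits under future adverse asthma outcomes. Measurement of secondary outcomes covers that group by severe exacerbations, systemic corticosteroid use and post-bronchodilator FEV1, and the Background discusses the adverse effects of long-term oral steroids. The phrase can fairly be read as the burden of asthma treatment, with steroid use as its proxy. The wording is unclear, not clearly in conflict.

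What the objection does not answer is the order of steps. The events are already elicited, the unrecorded ones cannot be retrieved, and the article itself uses the better order for serious events.

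**Conclusion.** The point holds as one of completeness and sensitivity. Non-serious events judged neither possibly device-related nor clinically significant are asked about and then not recorded, so the comparison of non-serious events by arm is incomplete and less able to show an unsuspected effect. The loss cannot be sized from the article. If the screen kept 75% or 50% of an event with true rates of 15% and 33%, power would be about 65% or 43% in place of 82%. This assumes 100 evaluable participants per arm and equal retention in both arms. The much lower figures at 25% or 10% retention are arithmetically right, but nothing in the article shows that so few events would pass, so they do not support a claim that most sensitivity is lost. Neither the sample size nor the primary analysis is affected.

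**What to change.** In Safety reporting:

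- Record every non-serious adverse event already elicited, other than the listed asthma events captured as outcomes.
- Hold attribution and severity as data fields.
- Use attribution only for classification as a device effect (ADE or SADE) and for expedited reporting, not as a condition of recording.
- For the DSMC, tabulate all adverse events and device-attributed adverse events by arm.

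This needs a wording change and more lines on the case report form. No visit or procedure is added, because the question is already put at each follow-up visit. The real cost is data entry and coding over 12 months in 222 participants with severe asthma.

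If the sponsor prefers to keep the screen, two wording changes are needed. The safety conclusion on non-serious events should be limited to those recorded, that is, the possibly device-related or clinically significant ones. And Secondary aims should make clear that side-effects of treatment are assessed only through systemic corticosteroid use, as in Measurement of secondary outcomes.

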### Statistics

The study will be reported in accordance with the Consolidated Standards of Reporting Trials statement and ICH Guidelines for Good Clinical Practice. All study data will be managed by ORTU using a bespoke database created using OpenClinica Enterprise Edition software (OpenClinica LLC, Waltham MA, USA). Confidentiality of participant data will be assured according to GCP.

### Sample size

Based on an estimated rate of two severe asthma exacerbations per participant over the 12-month period in the placebo group, a minimum of 222 participants (111 per group) will be required to provide 80 % power (at 5 % two-sided significance level) to detect a clinically meaningful 25 % reduction in the average exacerbation rate in the group using the TLA device.

This sample size is based on a Poisson regression model, with the treatment group as the covariate and a 10 % overall dropout rate. A review of comparative interventions of proven efficacy in severe asthma gave effect sizes ranging from 21 to 63 %, with a mean of 41 %. Given that this is a pragmatic trial where we expect our intervention to be less effective than an efficacy trial, we have chosen a deliberately more conservative effect size of 25 %. This represents on average, one less severe exacerbation every 2 years.

### Clinical outcomes analysis

The primary statistical analysis will be carried out on the basis of intention-to-treat (ITT). The primary efficacy endpoint in this study, the rate of clinically significant exacerbations over the 12-month period, will be analysed using a Poisson regression model to compare the rate of asthma exacerbations between the two groups with log of time used as an offset variable. Further analysis will adjust for the baseline characteristics including the ACQ score, age, body mass index (BMI) and sex.

Continuous secondary endpoints which involve repeated measures at baseline, 3, 6, 9, and 12 months (including measures of lung function, composite asthma control scores and health-related quality-of-life measures) will be analysed using longitudinal analysis methods, including mixed effect models to determine any effect of the TLA device over time. Continuous variables with only baseline and 12 months data, (including lung function and carer quality of life measures) will be analysed by analysis of covariance (ANCOVA) of the 12-month outcome adjusted where appropriate for baseline, minimisation factors and other important factors as detailed for the primary outcome.

Kaplan–Meier curves and log-rank test will be used to compare the time to first asthma exacerbation between the two groups. Cox proportional hazards models will be used to evaluate the effect of TLA device on the time to first asthma exacerbation, adjusting for the same covariates as in the primary analysis. Since the analysis of only time to first exacerbation leaves out much of the data, analysis incorporating multiple time-to-event (recurrent exacerbations) methods will also be used, including the Andersen–Gill extension.

The proportion of participants experiencing severe exacerbations over the 12-month follow-up period will be compared using a continuity-corrected Chi-squared test. The duration of severe exacerbations, the total number of days in an exacerbation state over the 12-month follow-up period, and the number of health care utilisations will be compared between the two groups using two-sample independent t-tests.

Exploratory sub-group analyses will include an assessment of factors associated with an improved treatment response including objective markers of bronchial and systemic allergy and inflammation, lung function, asthma and rhinitis control, quality of life and level of indoor air quality. The predictive effect of the biomarkers on exacerbations will be assessed by including the biomarker as an independent covariate together with the biomarker-treatment interaction using Poisson regression modelling in a multivariate framework (as described for the primary outcome).

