### Randomisation and blinding

Participants will be assigned with a random element in a 1:1 ratio between the intervention and control groups using a centralised randomisation system, Sealed Envelope™. A nondeterministic minimisation algorithm will be used to facilitate balanced allocation of participants across the two treatment groups for 1) clinical site, 2) prevalent vs. incident case and the following prognostic factors at baseline: 3) exacerbation frequency in the previous 12 months (2, 3, or ≥3), 4) use of oral corticosteroids (yes/no) and 5) pre-bronchodilator FEV1 (>50 % predicted yes/no).

Sealed Envelope™ will have been provided with a list of TLA product serial numbers by the manufacturing team based in Sweden and will allocate a specific TLA product to the participant. A secure e-mail notification will be sent immediately to the local trial team to confirm randomisation. A secure e-mail will be sent to the UK-based engineering team. This will include the participant’s trial number, TLA product serial number, and an exclusive, password protected, link for the engineering team to log in and access the participant’s contact details. The engineering team will then contact the participant (within 72 hours of Randomisation Visit 2) to arrange device delivery and installation without disclosing the treatment allocation to the participant. All study team members and the participants will be blind to which device they have received.

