### Measurement of primary outcome

The primary outcome, severe asthma exacerbations, are defined according to ATS/ERS guidelines [25] as a worsening of asthma requiring systemic corticosteroids ≥ 30 mg prednisolone or equivalent daily (or ≥ 50 % increase in dose if maintenance 30 mg prednisolone or above), for 3 or more days. Courses of corticosteroids separated by ≥ 7 days will be treated as separate severe exacerbations. Based on this, an ‘exacerbation-dose’ of systemic corticosteroids is defined as ≥ 30 mg prednisolone or equivalent daily if not on a maintenance systemic corticosteroid treatment or ≥ 50 % increase in dose if maintenance dose is 30 mg prednisolone or above.

Participants will be asked to start an exacerbation diary when starting an ‘exacerbation-dose’ of systemic corticosteroids (participant specific ‘exacerbation-dose’ is defined at Randomisation Visit 2). The exacerbation diary will include PEF measurements (using the trial electronic PEF device), oral corticosteroid dose, reliever medication use, and nocturnal asthma symptoms. Participants will be asked to report severe exacerbations to their local site trial team as soon as possible after onset via a dedicated telephone line or a secure NHS e-mail account. Wherever possible, participants will be asked to attend an exacerbation review with their local trial team within 72 hours to corroborate the exacerbation, at which the local trial team will complete the case report form (CRF) using the exacerbation diary. The definition of a severe asthma exacerbation with *any one* of the following additional criteria must be met:An associated decrease in morning PEF compared to maximum morning PEF achieved at baseline.A 50 % increase in reliever medication on at least 2 of 3 successive days compared to baseline.Increased nocturnal wakening.

If participants are not able to attend for an exacerbation review, the exacerbation diary will be collected at the next follow-up visit.

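### The primary Poisson model and the sample size both assume no extra-Poisson variation; if exacerbation counts are overdispersed, the 5% test is anti-conservative and the 80% power does not hold

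*Protocol article*

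**What the plan says.** Under Clinical outcomes analysis, the primary endpoint "will be analysed using a Poisson regression model to compare the rate of asthma exacerbations between the two groups with log of time used" as the offset. Covariates come in the next sentence: "Further analysis will adjust for the baseline characteristics including the ACQ score, age, body mass index (BMI) and sex". The sub-group paragraph of the same section returns to the model for biomarker-by-treatment interactions, "using Poisson regression modelling in a multivariate framework (as described for the primary outcome").

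Under Sample size, the inputs are an "estimated rate of two severe asthma exacerbations per participant over the 12-month period in the placebo group", 80% power at a two-sided 5% level "to detect a clinically meaningful 25 % reduction in the average exacerbation rate in the group using the TLA device", and 10% dropout, giving 222 participants (111 per group). The basis is stated: "This sample size is based on a Poisson regression model, with the treatment group as the covariate".

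The endpoint is a recurrent count. Measurement of primary outcome says: "Courses of corticosteroids separated by ≥ 7 days will be treated as separate severe exacerbations". Randomisation and blinding lists, among the "prognostic factors at baseline: 3) exacerbation frequency in the previous 12 months", followed by oral corticosteroid use and pre-bronchodilator FEV1. The article mentions no negative binomial or quasi-Poisson model, scale parameter, robust variance or dispersion check.

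**The concern.** A Poisson model sets the variance of each participant's count equal to its mean, given the covariates in the model. With treatment alone in the model, everyone in an arm must share one underlying rate. The protocol's own design expects otherwise. It balances the arms on factors it calls prognostic, it admits anyone with two or more exacerbations in the previous year with no upper limit, and it counts steroid courses as little as 7 days apart as separate events, so one unstable participant can contribute several correlated events.

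When rates vary between participants, the Poisson standard error reflects only the number of events and misses the between-participant part. The p-value is then too small and the interval too narrow, and the error favours declaring an ineffective device effective. This is the primary confirmatory test.

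**Working it through.** **Inputs from the article:** rates 2.0 (placebo) and 1.5 (TLA) per year, so rate ratio 0.75 and ln(0.75)² = 0.0828; two-sided 5% (z = 1.960); 80% power (z = 0.842); 1:1 allocation; 10% dropout.

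**Assumption:** negative binomial dispersion k, with variance = mean + k × mean², over 0.1 to 1. The article gives no value.

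**1. Reproduce 222.** The Signorini formula for Poisson regression with a binary covariate is N = (z_α√V0 + z_β√V1)² / (2 × ln(0.75)²), with V0 = 4 and V1 = 2 + 2/0.75 = 4.667. This gives (1.960 × 2 + 0.842 × 2.160)² / 0.1655 = 198.9, so 199 in total. Then 199/0.9 = 221.1, rounded up to 222, which matches including dropout. The Wald log-rate formula gives 110.6, so 111 per group, before dropout. Both use variance = mean, so 222 contains no allowance for overdispersion.

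**2. Type I error of the plain Poisson test.** At rate 2 in both arms the true variance is 1 + 2k times the Poisson variance. The actual error is 2 × [1 − Φ(1.96/√(1 + 2k))], and an honest interval is √(1 + 2k) times as wide.

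**3. Power of a valid analysis.** The variance of the log rate ratio is (1/2.0 + 1/1.5 + 2k)/n per group. Power is Φ(0.2877/SE − 1.96). For example, at k = 0.25 and n = 111, SE = √(1.6667/111) = 0.1225 and power = Φ(0.388) = 65%.

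| k | Type I error, formula | Type I error, simulated | Width factor | Power, 111 per group followed | Power, 100 per group followed |
|---|---|---|---|---|---|
| 0 | 5% | 5.1% | 1.00 | 80% | 76% |
| 0.1 | 7.4% | 7.1% | 1.10 | 74% | 69% |
| 0.25 | 11.0% | 10.4% | 1.22 | 65% | 61% |
| 0.5 | 16.6% | 16.4% | 1.41 | 54% | 50% |
| 1 | 25.8% | 25.1% | 1.73 | 40% | 37% |

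The simulation used 20,000 null trials per row with 111 per arm, mean 2 and 10% dropout at uniformly distributed times. In the same trials a sandwich variance gave 5.1% to 5.5% throughout. Coverage of the nominal 95% interval under the null is 100% minus the formula error: about 93%, 89%, 83% and 74% for the four non-zero values of k.

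**4. What k means here.** If half the participants average one exacerbation a year and half average three, the mean is 2 and the variance of the underlying rates is 1, so k = 1/2² = 0.25. That split is enough for an error of about 11%.

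**5. Size needed for 80% power.** Extending the formula in step 1 with V0 = 4(1 + 2k) and V1 = 4.667 + 8k, and dividing by 0.9, gives totals of about 264, 327, 432 and 643 for k = 0.1, 0.25, 0.5 and 1.

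**The case against.** The strongest reply is that the article names a regression family and an offset but does not say that model-based standard errors will be used. Poisson regression with a sandwich variance is still Poisson regression, and a condensed article can leave the variance estimator to an analysis plan that is not shown. It stands that such a plan may already deal with this. But the article names Poisson for the sizing, the primary test and the interactions, and its sample size is computed on pure Poisson variance. Followed as written, that gives the plain Poisson test.

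A reader might infer that treatment is certainly the only covariate in the primary analysis. The documents do not settle that: the statement comes from the sizing model. The primary sentence names no covariates and adjustment is placed in a further analysis, yet the Cox and ANCOVA plans refer back to covariates of the primary analysis, and the sub-group paragraph speaks of a multivariate framework. Adjusting for the minimisation factors would absorb part of the heterogeneity. How much cannot be calculated, because the article gives no effect sizes for them, and adjustment leaves unexplained variation between participants untouched.

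A reader might also infer that the p-value is bound to be too small. That is not supported either. The minimisation factors show that participants are expected to differ, not by how much; the eligibility criteria narrow the population; and at k = 0 the test is valid.

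The log-rank, Cox and chi-squared analyses do not rely on Poisson variance and might show up a result driven by a few frequent exacerbators, but they do not repair the primary test.

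**Conclusion.** The point holds in conditional form. The article fixes a primary model and a sample size that both set variance equal to mean, while its own design expects participants' rates to differ. If counts are overdispersed, the direction of the error is certain: the test is anti-conservative. Its size depends on a k that the documents do not give: about 7% to 25% true type I error for k from 0.1 to 1 at a mean of 2 per year, against the stated 5%. These figures assume negative binomial counts and no covariate adjustment. The 80% power claim rests on the same absence of overdispersion.

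**What to change.** Before unblinding, state that the primary analysis is a negative binomial regression, or a Poisson regression with robust (sandwich) variance, with log follow-up time as offset. Use the same approach for the exploratory biomarker interactions. The choice must be made in advance, since picking the variance after seeing the results would be open to challenge. A negative binomial interval relies on its variance form being right; the sandwich variance does not, and in the simulation it lost nothing material at k = 0.

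The wording is one sentence and needs no new data, but it would be wrong to call the change free. Intervals widen by the factors in the table, and the stated 80% power no longer holds once k exceeds zero. Power for 222 participants should therefore be restated over a range of k, with the formula and the number followed made explicit.
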